## 2. Research Hypothesis

We hypothesize that after the intervention, women with GDM who receive the intervention program designed based on BCW will have (1) higher scores of self-management behavior and self-efficacy, (2) better results of maternal glucose metabolism, and (3) lower incidences of common adverse pregnancy outcomes than women with GDM who receive general dietary management.

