### 3.5. Sample Size

Due to the lack of prior data about applying BCW in dietary intervention in women with GDM, a pilot study will be carried out to provide a comprehensive estimate of the effect size of the intervention. The recruitment goal of the pilot study is 30 pregnant women with GDM for each group [29]. No a priori hypotheses of effect size to identify the ineffectiveness of a comprehensive study were proposed since we considered that the available data were insufficient to create these meaningfully. The minimum sample size for the future study will be calculated based on the results of the pilot study.

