## 4. Measures

Primary outcomes for compliance with dietary recommendations include self-management behaviors and self-efficacy of dietary control, and the average daily GL value. Secondary outcomes for maternal glucose metabolism include results of OGTT, FBG, 2 h PBG, and HbA1c. Secondary outcomes for adverse pregnancy outcomes include non-normal gestational weight gain (GWG) (excessive GWG or insufficient GWG), insulin use during pregnancy, cesarean section, premature delivery, macrosomia, and fetal intrauterine growth restriction. The timeliness of data collection is shown in Table 2.

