## 6. Statistical Analysis

All quantitative analysis will be conducted through IBM SPSS Statistics 24.0 software (IBM Corp. Released 2016. IBM SPSS Statistics for Windows, Version 24.0., IBM Corp.: Armonk, NY, USA). The baseline characteristics of participants will be presented by descriptive statistics. The continuous variables will be described by means and standard deviation, or medians and quartiles. The frequencies (N) and percentages (%) will be used for categorical variables. The analysis of variance (ANOVA), Kruskal–Wallis, test or Chi-square test will be used to describe the mean differences of continuous variables and categorical variables between the two groups at baseline. The explored assessment will be analyzed by repeated measures multivariate analysis of variance (MANOVA), and then the post-hoc pairwise comparison will be made. Effect sizes were calculated with Cohen’s d. P value of 0.05 will be considered the significant level for all outcomes.

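### One 0.05 level is applied to three unranked primary outcomes and ten secondary outcomes, with no adjustment, ranking or joint-success rule, in a trial described as a pilot

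*Protocol article*

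**What the plan says.** Section 4 (Measures) sets the primary outcomes: "Primary outcomes for compliance with dietary recommendations include self-management behaviors and self-efficacy of dietary control, and the average daily GL value". That makes three, with no order of importance.

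The secondary outcomes come in two groups. For glucose metabolism: "Secondary outcomes for maternal glucose metabolism include results of OGTT, FBG, 2 h PBG, and HbA1c". For pregnancy: "non-normal gestational weight gain (GWG) (excessive GWG or insufficient GWG), insulin use during pregnancy, cesarean section, premature delivery, macrosomia, and fetal intrauterine growth restriction". That is four plus six, so ten.

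Section 6 (Statistical Analysis) gives one decision rule: "P value of 0.05 will be considered the significant level for all outcomes". On method it says: "The explored assessment will be analyzed by repeated measures multivariate analysis of variance (MANOVA), and then the post-hoc pairwise comparison will be made". It does not make the pairwise comparisons conditional on the MANOVA and names no adjustment for them.

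The first hypothesis in Section 2 expects "higher scores of self-management behavior and self-efficacy". Average daily glycemic load (GL), the third primary, appears in none of the hypotheses.

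Section 3.5 describes the trial as a pilot meant to supply an effect size for a later study: "The recruitment goal of the pilot study is 30 pregnant women with GDM for each group". The Abstract and Section 8 nevertheless discuss what would follow if the program turns out to be effective.

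**The concern.** The 0.05 rule is stated for every outcome, so this is a rule fixed in the text and not just a detail left out. With three unranked primaries and no requirement that they succeed together, a report that follows the text could rest a positive conclusion on whichever primary fell below 0.05. The ten secondaries carry the same threshold and so the same apparent weight.

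Two things are at stake. First, the chance of a spurious significant finding exceeds the stated 5%. Second, a study of 30 women per group, sized without a power calculation and intended to inform a later trial, could be read as having shown efficacy. The mismatch between Hypothesis 1 and the primary list adds doubt about which outcomes the main claim is meant to rest on.

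**Working it through.** **Inputs from the protocol article**
- Level per outcome: 0.05 (Section 6). Sidedness is not stated; two-sided is assumed.
- Primary outcomes: 3. Secondary outcomes: 4 + 6 = 10. Total: 13 (Section 4).
- Group size: 30 per arm (Section 3.5).
- Correlation between outcomes: not given. A common correlation from 0 to 0.9 is assumed.

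The article gives no overall error rate or power, so there is no figure of its own to reproduce beyond the 0.05 for one test.

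**Any false result, either direction, independent outcomes:** 1 − 0.95^k
- k = 3: 1 − 0.95^3 = 0.143 (upper bound under any dependence: 3 × 0.05 = 0.15)
- k = 10: 1 − 0.95^10 = 0.401
- k = 13: 1 − 0.95^13 = 0.487

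**False results favouring the intervention only, two-sided tests, independent outcomes:** 1 − 0.975^k
- k = 3: 1 − 0.975^3 = 0.073
- k = 13: 1 − 0.975^13 = 0.281

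For a single test the comparator here is 2.5%, not 5%.

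**Correlated outcomes** (simulated equicorrelated normal test statistics, 1,000,000 draws)

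| Correlation | 3 primaries, either direction | 3 primaries, favourable only | 13 outcomes, either direction | 13 outcomes, favourable only |
|---|---|---|---|---|
| 0 | 14.3% | 7.3% | 48.7% | 28.0% |
| 0.5 | 12.5% | 6.3% | 33.4% | 16.8% |
| 0.8 | 9.8% | 4.9% | 19.1% | 9.6% |
| 0.9 | 8.4% | 4.2% | 13.8% | 6.9% |

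**How firm the count of 13 is.** Section 4.4 has the OGTT repeated at 37 weeks, while Table 2 marks it at enrollment only. Without a follow-up OGTT there are 12 outcomes: 1 − 0.95^12 = 0.460. Counting excessive and insufficient weight gain separately gives 14: 1 − 0.95^14 = 0.512. Rare binary outcomes do not use their full 5%: with 30 per arm the chi-square test has a true size of about 2.8% at an assumed 5% event rate and 1.0% at 3%.

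**Would the MANOVA protect the primaries if it were a gate?** This was simulated with Hotelling's T² on three outcomes, 30 per arm and 40,000 draws, followed by unadjusted t tests at correlations 0 to 0.8. When nothing differs, the chance of a false claim is 3.1% to 4.6%. When one primary truly differs (by 1.2 standard deviations in the simulation), the chance of a false claim on the other two is 7.9% to 9.7%. A gate would therefore help only when nothing differs.

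**After the fix.** Holm's first step tests the smallest p-value at 0.05/3 = 0.0167. With three independent nulls the overall error is 1 − (1 − 0.0167)^3 = 4.9%. A single named primary at 0.05 gives 5%.

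**The case against.** The strongest reply is that this is a pilot. Section 3.5 disclaims any prior effect size, Section 6 itself speaks of an explored assessment, and strict familywise control is a standard for confirmatory trials. That lowers the weight of the point but does not remove it. The text nowhere says that significant results are exploratory, and it keeps directional hypotheses and language about the program proving effective. If the study only estimates effects, a significance rule for every outcome is even less apt.

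A second reply is that a success rule or multiplicity method may sit in an analysis plan that is not shown. It may, but such a plan would have to depart from the published statement that 0.05 applies throughout.

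A third is that Section 8 mentions compliance, glucose metabolism and pregnancy outcomes together. If all had to succeed there would be no inflation. That is a fair reading of the sentence, but no section makes it a decision rule. Equally, no section says that one significant primary suffices, so the figures above are conditional on that use.

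A reader might go further and infer that self-efficacy should not be a primary, or that the two questionnaires are prone to bias while GL is not. The documents do not support this. Treating self-efficacy as a compliance outcome is a choice of construct, made consistently in Sections 2 and 4. GL comes from participants' own 24-hour dietary records (Section 4.3), so it too is self-reported by unblinded women. Section 7 already concedes reporting bias and an unvalidated questionnaire.

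**Conclusion.** The point holds in a bounded form. Following Section 6 as written, and counting any significant primary as success, the two-sided false-positive chance over the three primaries is about 8% (correlation 0.9) to 14% (independence). Counting only results in favour of the intervention, it is 7.3% under independence, about 5% at correlation 0.8 and 4.2% at 0.9. If the directional hypotheses were tested one-sided at 0.05, the independent figure would return to 14.3%.

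A reader might take 14.3% as the chance of a false claim of benefit, or 49% as the trial's error rate. Neither is supported. The first counts results favouring control as well. The second needs independence, which is implausible among related glucose measures and insulin use; it also needs a follow-up OGTT on which the article disagrees with itself, and full 5% size for rare binary events. Across all outcomes the error is higher than for the primaries alone, but 49% is an upper figure.

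The rule is worth correcting because it conflicts with the pilot aim and leaves the basis of any efficacy claim open. It does not invalidate the trial.

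**What to change.** In Section 6, replace the statement that 0.05 applies to every outcome with a rule limited to the primary family, in one of two forms:
- name one primary outcome, measured at 37 weeks, tested at two-sided 0.05; or
- keep all three and test them with Holm at an overall two-sided 0.05 (ordered p-values against 0.0167, 0.025 and 0.05).

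Report the secondary outcomes as estimates with 95% confidence intervals and label them exploratory, in line with the pilot aim in Section 3.5. Bring Hypothesis 1 in Section 2 into line with the primary list in Section 4, which includes GL.

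The cost is wording in Sections 2, 4 and 6. No participants or measurements are added. The downside is a slightly stricter threshold if three primaries are kept, and fewer outcomes that can be called significant. The change should be made before results are known.

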## 7. Discussion

This randomized controlled trial is designed specifically for women with GDM to achieve effective blood glucose control by strengthening GDM women’s compliance with dietary recommendations. To our knowledge, this is the first study to use the BCW model as the theoretical framework for dietary intervention in women with GDM. Compared with other nutritional interventions for GDM women, this study identifies one or more effective intervention functions of three essential conditions in COM-B system and links interventions to BCTs, so as to avoid the omission of important interventions. Furthermore, the impact of environmental factors on behavior was considered in this study. For example, the intervention object is not limited to women with GDM, but also includes pregnant women’s main caregivers. The capability and motivation of primary caregivers to assist women with GDM in managing their diet can also be improved through the intervention. Women with GDM can get more family support which will create more opportunities for women with GDM to control their diet according to dietary recommendations so as to achieve better results in controlling blood glucose. Women with GDM can receive more family support, which will create more opportunities for women with GDM to comply with dietary recommendations, thus achieving better glycemic control.

It is worth noting that the study still has some limitations. First, dietary management behaviors and self-efficacy of women with GDM are evaluated through several self-reported questionnaires, which may cause reporting bias. Second, a questionnaire measure used in this study is not validated. Further testing in a larger sample of patients with GDM is needed. Third, researchers will be involved throughout the study, which may lead to the subjective bias of the subjects or personnel, thus affecting study results.

## 8. Conclusions

Nevertheless, it remains exciting if this intervention program designed with BCW proves effective in improving compliance with dietary recommendations and maternal glucose metabolism and reducing adverse pregnancy outcomes. The success of this intervention will provide medical professionals with a novel intervention design idea that BCW can also be applied to improve other self-management behaviors in women with GDM, such as improving compliance with glucose self-monitoring and physical activity. This may provide a boost to the clinical management of GDM.

## Figures and Tables

**Figure 1 ijerph-19-10726-f001:**
[figure not shown]
Behavior Change Wheel (adapted from Michie et al. [25]).

**Table 1 ijerph-19-10726-t001:** Matrix of links between the components of the BCW model (COM-B model, intervention functions, and policy category) for the intervention.

Mode of Delivery	Time	Intervention Subjects	Policy Category	Intervention Functions: Description of Intervention Strategies	Capability		Opportunity		Motivation	
					Phys	Psych	Social	Phys	Refl	Aut
Individual primarily consultation	At enrollment	Pregnant women	Communication; Guideline;	*Persuasion*: Identify the positive and negative aspects of current dietary behaviors, and inform about the benefits of adjusting dietary behaviors;					√	√
			Communication; Guideline;	*Education*: Set goals of blood glucose control and clarify the importance and principles of dietary management for GDM, Explain the content of paper guidance materials,		√			√	
			Environmental planning	*Environment restructuring*: Provide paper guidance materials for designing daily recipes. Show the food atlas, and provide sample food scales to pregnant women for determining the amount of food intake;			√	√		√
			Communication; Guideline;	*Training*: Guide pregnant women in designing daily recipes	√	√		√		√
Online consultation	At three days after enrollment	Pregnant women	Communication;	*Incentivisation and enablement*: Evaluate the dietary behaviors of pregnant women in the past three days and correct the wrong dietary behaviors;	√	√	√	√	√	√
		Pregnant women’s main caregivers	Communication; Guideline;	*Education, persuasion and environment restructuring*: Inform the main caregivers about the importance of dietary management for women with GDM and the benefits of providing good family support that can enhance the motivation of pregnant women to adhere to MNT;		√	√	√	√	√
		Pregnant women	Communication; Guideline;	*Persuasion and enablement*: Put forward some suggestions on how to manage the diet when eating out or eating at home;	√	√	√	√	√	√
	At 7:00 pm every Friday	Pregnant women	Service provision; Communication;	*Enablement*: Provide the online guidance team to answer pregnant women’s questions and conduct health education as the control group, and help pregnant women design recipes for the next week’s diet.	√	√	√	√	√	√
The first additional consultation at review	At one week after enrollment	Pregnant women	Communication; Guideline; Service provision;	*Persuasion, incentivization, and enablement*: Re-measure blood glucose, and look back and analyze the dietary-related reasons for the positive or reverse results of controlling blood glucose	√	√	√	√	√	√
			Communication;	*Education, persuasion, and modeling*: Set up the three-person cooperation group to achieve peer education		√	√		√	√
The second additional consultation at review	At 28 weeks of gestation	Pregnant women	Communication;	*Education*: Recalculate total daily energy requirements, and adjust exchange servings of a certain food for meeting the need for the healthy pregnancy		√			√	

**Table 2 ijerph-19-10726-t002:** Timeliness of Data Collection.

	Enrollment	A Week after Enrollment	28 Weeks of Gestation	37 Weeks of Gestation	After Intervention (Before Delivery)	After Delivery
**Baseline Characteristics**						
Demographic characteristics	√					
Pregnancy-related characteristics	√					
**Body Characteristics**						
Weight	√				√	
Height	√					
**Maternal Glucose Metabolism**						
75 g OGTT	√					
FBG		√		√		
2 h PBG		√		√		
HbA1c		√		√		
**Compliance with Dietary recommendations**						
Self-management behavior				√		
Self-efficacy				√		
Average daily GL value			√	√		

Abbreviations: 75 g OGTT, 75 g oral glucose tolerance test; FBG, fasting blood glucose ; 2 h BG, 2 h postprandial blood glucose; GL, glycemic load.

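### Two of the three primary outcomes are scored only once, at 37 weeks, so the repeated-measures analysis in Section 6 cannot be computed for them and no enrollment score is available for adjustment

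*Protocol article*

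**What the plan says.** Section 4 (Measures) states: "Primary outcomes for compliance with dietary recommendations include self-management behaviors and self-efficacy of dietary control, and the average daily GL value". For timing it refers the reader on: "The timeliness of data collection is shown in Table 2".

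Table 2 has six columns: enrollment, one week after enrollment, 28 weeks, 37 weeks, after the intervention but before delivery, and after delivery. In the block on compliance, the rows "Self-management behavior" and "Self-efficacy" each carry one tick, under 37 weeks. The row "Average daily GL value" carries two, under 28 and 37 weeks. None of the three is ticked at enrollment. Section 4.3 describes both questionnaires without giving any other time. Section 4.2 limits the enrollment questionnaires to demographic and pregnancy-related items.

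Section 6 gives one method for outcomes: "The explored assessment will be analyzed by repeated measures multivariate analysis of variance (MANOVA"), followed by post-hoc pairwise comparison. Section 2 predicts that, after the intervention, women in the intervention arm will have "higher scores of self-management behavior and self-efficacy" than women under general dietary management.

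**The concern.** A repeated-measures analysis needs at least two measurements per woman, and two of the three primary outcomes have one. Whoever analyzes the trial would have to choose another method for them, and the article names none. The missing enrollment score also rules out the usual way of sharpening a between-arm comparison of a questionnaire score.

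This matters because Section 3.5 makes the study a pilot whose purpose is to estimate the effect size from which the sample size of the future study will be calculated. The precision of that estimate is the main thing the pilot has to deliver.

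**Working it through.** **Step 1: count time points.** From Table 2:

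| Primary outcome | Times ticked | T |
|---|---|---|
| Self-management behavior | 37 weeks | 1 |
| Self-efficacy | 37 weeks | 1 |
| Average daily GL | 28 and 37 weeks | 2 |

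The table does not look damaged in extraction: each row has six cells, and the ticks in other rows fall in sensible columns (OGTT at enrollment; FBG at one week and 37 weeks).

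**Step 2: degrees of freedom.** With two arms, the time effect has T − 1 degrees of freedom and arm-by-time has (2 − 1)(T − 1).
- T = 1: 0 and 0. The analysis cannot be computed for the two questionnaire scores.
- T = 2: 1 and 1. It can be computed for GL, although both GL values come after randomization.

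**Step 3: what an enrollment score would add.** The article states no power, effect size or correlation, so there is no figure of its own to reproduce.

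Inputs from the article: n = 30 per arm (Section 3.5), 1:1 allocation (Section 3.7), significance level 0.05 (Section 6).

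Assumptions: two-sided test; true standardized difference d = 0.5; correlation r between the enrollment and 37-week scores.

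Formulas:
- Adjusting for the enrollment score multiplies the residual SD by √(1 − r²), so the effective difference is d/√(1 − r²).
- Noncentrality = √(30/2) × d/√(1 − r²), on 58 degrees of freedom without the covariate and 57 with it.
- 95% CI half-width in SD units ≈ 1.96 × √((2/30)(1 − r²)).
- Equivalent n per arm without adjustment = 30/(1 − r²).

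For the 37-week score alone, noncentrality = √15 × 0.5 = 1.94 and half-width = 1.96 × √(2/30) = 0.51. For r = 0.5, noncentrality = 1.94/√0.75 = 2.24 and half-width = 0.51 × √0.75 = 0.44.

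| Analysis | Power at d = 0.5 | CI half-width | Equivalent n per arm |
|---|---|---|---|
| 37-week score only | 48% | 0.51 | 30 |
| Adjusted, r = 0.1 | 48% | 0.50 | 30 |
| Adjusted, r = 0.2 | 49% | 0.50 | 31 |
| Adjusted, r = 0.3 | 51% | 0.48 | 33 |
| Adjusted, r = 0.5 | 59% | 0.44 | 40 |

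**Step 4: which r is plausible for which score.** The last two of the five self-management items ask about following the exchange strategy that staff recommended and about consulting GL values. The food exchange table that shows GL values is handed out at enrollment (Section 3.8), so before instruction these items should be near zero for almost everyone. With part of the score at its floor, r may be below 0.3, and the upper rows of the table are then the relevant ones. The C-DMSES nutrition subscale asks about confidence, and this argument does not apply to it.

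**The case against.** The strongest reply is that the sentence in Section 6 does not name the outcomes it covers. It cannot cover all of them, since cesarean section and macrosomia are yes/no events, and it does fit FBG, 2 h PBG, HbA1c and GL, which are each ticked twice. A simple two-group test for a single score could be left to a fuller plan. It is true that the sentence names no outcomes. But it is the only outcome method given, so either it is meant for these two scores and cannot be run, or two named primary outcomes have no stated method. Section 6 needs correcting in both cases. A one-time MANOVA across several outcomes is possible, but it is not a repeated-measures analysis.

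A second reply is that Table 2 may simply lack a tick. Section 4.4 says the glucose indicators are measured at study entrance, yet Table 2 shows no enrollment tick for FBG, 2 h PBG or HbA1c. An omission is possible. For the two questionnaires, however, nothing in the text points to an enrollment measurement.

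Three stronger readings are tempting, and the document does not support them:
- That a comparison without baseline scores is biased. Under 1:1 randomization it is not, and Section 2 predicts higher scores after the intervention, not greater change.
- That a chance difference between arms at the start is an additional harm. It is already contained in the standard error of the 37-week comparison.
- That the planned baseline comparison fails. Section 6 promises it for baseline characteristics, which Section 4.2 defines without the primary outcomes.

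**Conclusion.** The point holds. As printed, the only stated outcome analysis cannot be computed for self-management behavior and self-efficacy, and no enrollment score is available for adjustment. This first part follows from Table 2 and Section 6 and needs no assumption beyond taking Table 2 as complete.

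The size of the precision loss does rest on assumptions. With 30 per arm and d = 0.5, baseline adjustment would raise power from 48% to about 51% at r = 0.3 and 59% at r = 0.5, and the article gives neither d nor r. The gain is expected mainly for self-efficacy and may be negligible for the self-management score. In a pilot the narrower confidence interval matters more than the power figure.

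**What to change.** 1. In Table 2, add the nine-item C-DMSES nutrition subscale and the five-item self-management questionnaire under enrollment for both arms. They should be completed after consent and before allocation is disclosed and any dietary instruction is given.
2. In Section 6, for these two scores, replace the repeated measures MANOVA by one linear model each: 37-week score on arm plus enrollment score. Report the adjusted mean difference with its 95% confidence interval, and Cohen's d based on the unadjusted SD.
3. If the enrollment measurement is not added, state in Section 6 a two-group comparison of each score at 37 weeks with a 95% confidence interval.

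The cost is one amended table, a few sentences in Section 6, and a few extra minutes per woman at a visit where questionnaires are already completed. Item 3 costs only the sentences. The enrollment score cannot be recovered once a woman has been instructed, so items 1 and 2 have to be in place before recruitment.
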